#### Sample size

The sample size has been estimated using Epidat 4.2. A one-sided approach has been assumed with a confidence level of 95% and a statistical power of 80%. It has been decided to take equal sizes in the two groups (i.e. R = n2/n1) and the Yates correction will not be applied. The sample size calculation was based on the results of a similar RCT, specifically the study conducted by Fernández et al. in 2018 [16] which compared the outcomes of a traditional cognitive stimulation intervention versus an intervention based on everyday cognition. The primary variable chosen in both studies was everyday cognition. The study found that the experimental group (those who received everyday cognition training) demonstrated an improvement of 2.57 points in the primary variable, while the control group (those who received traditional cognitive stimulation) only demonstrated an improvement of 0.39 points. With an expected population loss of 20%, the final sample size was n = 99 participants, with 50 in the experimental group and 49 in the control group.

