### Procedures and data collection

#### Evaluations and study plan

Participants will be assessed at two points during the study: the baseline assessment at the beginning of the study and the final assessment after the end of the intervention. The baseline assessment will take place after recruitment and before randomisation and allocation of subjects to the corresponding group. This initial assessment includes the recording of the independent variables and the primary outcome variables to be studied; the intervening variables will be recorded and several objective assessment tests will be used. Then, after randomisation, the intervention for each group will be carried out. Then, another assessment will be carried out, considered the final assessment, where participants will be asked to complete the same objective tests as in the initial assessment. The results will be notified by means of an individual and personal report to those persons who expressed the wish at the beginning to receive the information corresponding to the results and evolution. All evaluations will be carried out by research staff, previously trained and instructed in this process. This process can be seen in more detail in Fig 2 which includes a flow chart of the study methodology.

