#### Description of the variables

The primary variable will be everyday cognition, measured by the Test for the Evaluation of Everyday Cognition (PECC) and cognitive performance, measured by the Montreal Cognitive Assessment Test (MoCA). Secondary variables will be functionality (Functional Independence Measure, FIM), emotional state (Yesavage Scale), frailty (Frailty Index) and independence in instrumental activities of daily living (Lawton and Brody Scale). We will also record the following intervening variables in the clinical history of each participant: social support (Questionnaire MOS) and adherence to treatment (Questionnaire ARMS-e), and other socio-demographic data (age, sex, level of education, marital status and main occupation).

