### Data analysis

To test the normal distribution of data, a histogram will be used. Variables that have a normal distribution shall be defined by the mean and standard deviation, while variables that do not follow a normal distribution shall be defined by the median and the interquartile range. The effects of the intervention on primary outcomes (everyday cognition and cognitive function) and secondary outcomes (functionality, emotional state, and fragility) will be examined through a two-way analysis of covariance (ANCOVA), with the intervention group (control or experimental) included as a fixed factor. The differences between initial results and those after intervention, as both the dependent variable and covariates, will include intervening study variables such as age, gender, education level, marital status and occupation. The difference in means will be calculated using Cohen’s d to evaluate effect size. Group differences in intervening variables will be analyzed using independent samples t-tests for continuous variables (e.g., age). The chi-square test will be used to investigate group differences in categorical variables (e.g. gender). Significant values will be considered for p-values less than 0.05, with a 95% confidence interval. IBM SPSS Statistics software version 28.0.1 will be used for statistical analysis”.

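### The ANCOVA sentence cannot be followed as printed, and on its most plausible reading the outcome's own baseline score is not named as a covariate

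*Protocol article*

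**What the plan says.** The Data analysis section says that effects on the primary and secondary outcomes "will be examined through a two-way analysis of covariance (ANCOVA), with the intervention group (control or experimental) included as a fixed factor". No second factor is named. The next sentence assigns the variables: "The differences between initial results and those after intervention, as both the dependent variable and covariates, will include intervening study variables", followed by examples, "such as age, gender, education level, marital status and occupation".

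The section Description of the variables makes PECC and MoCA the primary variables and lists the other scales as secondary. It defines the intervening variables as "social support (Questionnaire MOS) and adherence to treatment (Questionnaire ARMS-e), and other socio-demographic data". The outcome scales are not among them.

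The section Evaluations and study plan places the baseline assessment before randomisation and says: "This initial assessment includes the recording of the independent variables and the primary outcome variables to be studied". At the final visit "participants will be asked to complete the same objective tests as in the initial assessment". Completing the initial assessment is an inclusion criterion (Participants section), so every included participant should have baseline scores.

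**The concern.** This is the article's only statement of the primary analysis model, and it does not settle three things: what the dependent variable is, whether the baseline score of that outcome enters the model, and what the second factor of a two-way analysis would be. Models that could be fitted under this wording give different estimates and p-values for two primary variables. A protocol should fix that choice before the data are seen.

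The baseline score of the same scale is usually the strongest predictor of the final score. Leaving it out of a change-score model costs precision. It also lets a chance baseline difference between arms feed into the estimate through regression to the mean. That sensitivity matters more here because eleven intact groups are allocated, which leaves few units over which chance differences can average out.

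**Working it through.** **No figure in the plan to reproduce.** The article gives no SD and no baseline-to-final correlation r. The Sample size section gives only the mean improvements, 2.57 and 0.39 points (difference 2.18). The results below are therefore in SD units, with r assumed over a range.

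**1. The sentence as printed.** Let C = final − baseline and G = arm. Regressing C on G and C is solved exactly by coefficient 1 on C and 0 on G, whatever the true effect. A simulation (40 per arm, r = 0.6, true effect 0.5 SD, 2,000 runs) gave a mean group coefficient of 0.000 with no spread. This shows only that the sentence cannot be applied literally.

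**2. The most plausible reading.** C is the dependent variable, G the factor, and the covariates are socio-demographic. The covariate list is open-ended, but its members must be intervening variables, and their definition does not include baseline outcome scores.

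**3. Precision.** Take equal SDs (set to 1) at both visits and leave the socio-demographic covariates aside.

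- Change score: variance = 2(1 − r)
- Baseline-adjusted: residual variance = 1 − r² = (1 − r)(1 + r)
- Ratio, adjusted to change = (1 + r)/2

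The last column assumes that the change-score analysis has exactly 80% power at one-sided 5%, as in the Sample size section. It ignores clustering: power = Φ[(1.645 + 0.842)/√ratio − 1.645].

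| Assumed r | Change | Adjusted | Ratio | Variance saved | Power with adjustment |
|---|---|---|---|---|---|
| 0.5 | 1.00 | 0.75 | 0.75 | 25% | 89.0% |
| 0.6 | 0.80 | 0.64 | 0.80 | 20% | 87.2% |
| 0.7 | 0.60 | 0.51 | 0.85 | 15% | 85.4% |
| 0.8 | 0.40 | 0.36 | 0.90 | 10% | 83.5% |

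The same simulation agrees at r = 0.6. Both analyses were centred on the true 0.5 SD (mean 0.499 each). The empirical SE was 0.200 for change and 0.181 for the adjusted model, so the variance ratio was (0.181/0.200)² ≈ 0.82 against a theoretical 0.80.

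**4. Sensitivity to chance imbalance.** If one arm starts b SD higher, the change-score contrast is expected to move by −(1 − r)b.

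| Assumed r | b = 0.2 SD | b = 0.3 SD |
|---|---|---|
| 0.5 | −0.10 | −0.15 |
| 0.7 | −0.06 | −0.09 |
| 0.8 | −0.04 | −0.06 |

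These shifts are in SDs of the score. They apply to one realised allocation and average to zero over allocations.

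**5. Final score or change.** Once baseline X is a covariate, the choice does not affect the arm effect: Y − X = a + βG + cX is the same model as Y = a + βG + (c + 1)X. The defect is the missing baseline term, not the use of change as such.

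**The case against.** **The sentence is a slip.** Taken strictly it says that differences include age and gender, which has no meaning, so nobody would fit the difference as its own covariate. This stands. A reader might infer that the trial plans an analysis that must return zero; the text is too garbled to support that. It still has to be rewritten.

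**It may mean final score on initial score.** The sentence mentions two measurements and then two roles, so baseline-adjusted ANCOVA might have been intended. But its subject is the differences between the measurements, and the covariates it goes on to describe are intervening variables. The reading cannot be excluded, so it would be too strong to say that baseline is certainly left out. What can be said is that it is not named.

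**The list is open, and an analysis plan may exist.** True, but the list is limited to a class of variables that excludes baseline outcome scores. The article also fixes a model here rather than deferring it.

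**The harm is limited.** This stands. A reader might infer bias, but under randomisation the change score is unbiased on average, and it already uses baseline by subtraction. A reader might also infer that a large imbalance is likely. Suppose an ICC of 0.05, eleven groups of 9 and a 45 v 54 split, none of which the article states. The design effect is then 1 + 8 × 0.05 = 1.4 and the SE of the baseline difference is √[1.4(1/45 + 1/54)] = 0.239 SD. A difference beyond 0.3 SD then occurs in about 21% of allocations: possible, but not likely.

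**Conclusion.** The point holds as a defect of specification with a free gain in precision. The model sentence cannot be carried out as printed, and the two-way label has no second factor behind it. On the most plausible reading, no outcome is adjusted for its own baseline, although that baseline is collected before randomisation.

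The cost is moderate. Adjustment would cut residual variance by 10 to 25% for r from 0.8 down to 0.5. It would also remove a shift of 0.04 to 0.15 SD for a chance imbalance of 0.2 to 0.3 SD over the same range of r. These figures assume equal SDs at the two visits and values of r that the article does not give. The socio-demographic covariates may already recover part of the gain. The shift cannot be put as a share of the target effect, because no SD is stated. None of this shows a biased or inflated treatment effect.

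**What to change.** Replace the sentence in Data analysis with a specification that applies to each scale separately:

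- Dependent variable: final score (or change from baseline).
- Covariates: baseline score of the same scale, plus the five socio-demographic covariates already named there, as a closed list.
- Fixed factor: arm.
- Reported result: adjusted mean difference with its 95% CI.

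Delete the words that make the difference a covariate, and delete the two-way label. How to handle clustering by centre is a separate question, and this change does not settle it.

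The cost is one rewritten sentence, made before outcome data are analysed by arm. The baseline scores are already collected, so no visit, test or participant is added.

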### Ethical aspects

The study was approved by the Clinical Research Ethics Committee of the Area of Health of Salamanca (ID: PI 902) (S2 File) (S3 File), having obtained the prior written informed consent of the study subjects and in conformance with the Helsinki Declaration (S4 File). The participants will be informed of the objectives of the project and the risks and benefits of the interventions that will be carried out during the work. Participants will be fully informed, and we will guarantee that their data will be treated with the utmost confidentiality throughout the study and also after its completion. Consequently, data and information will not be shared with third parties. Researchers involved in the study will strictly adhere to professional confidentiality and the confidentiality of the participants will be guaranteed at all times in accordance with the laws on the protection of personal data and biomedical research presented in the provisions of Organic Law 3/2018 of December 5 on the Protection of Personal Data and the Guarantee of Digital Rights, Regulation (EU) 2016/679 of the European Parliament and Council of 27 April 2016 on data protection (GDPR), and under the conditions established by Law 14/2007 on biomedical research.

Significant modifications to the protocol (such as changes in the tools of evaluation, modifications to the selection criteria or to the interventions) will be communicated immediately to the Ethics Committee.

And since this is a randomised clinical trial, it follows the CONSORT guidelines, and it was registered. TRIAL REGISTRATION: ClinicalTrials.gov; ID: NCT05688163.

### Rigour

This study protocol has been developed following the evidence-based recommendations of the SPIRIT 2013 Statement [28] on the minimum content of a clinical trial protocol (S1 File). And the study design also follows the recommendations of the CONSORT 2010 [29] guidelines for the conduct of parallel-group randomized controlled clinical trials (RCTs).

The TIDieR checklist is added as a tool to describe and replicate the intervention proposal (S6 File).

Data availability: Upon completion of the study, the data collected here will be made available to those investigators who request it through FAIRsharing of research data repositories at https://www.re3data.org/.

## Discussion

The expected results of this study can be transferred to clinical practice, incorporating a specific assessment of everyday cognition, as well as a training programme for everyday cognition. This study aims to improve conventional clinical practice on the training of cognitive functions by proposing a new tool based on the importance of real cognitive functioning or everyday cognition, assessing and intervening on the cognition of older adults during the resolution of complex tasks in their daily lives, giving full priority to the main objective of occupational therapy, which is the gain in terms of autonomy and functionality, and thus improving the quality of life of older adults.

We would like to highlight the importance of promoting the use and creation of assessment tests focused on everyday cognition from occupational therapy, as it gives a global vision of the person’s current occupational performance.

Furthermore, as we pointed out, we hope that the results of the study will solve shortcomings found in our daily clinical practice, with interventions based on traditional cognitive stimulation; such as problems in generalising the increase in scores or improvement of cognitive performance in the daily performance of older people. It is important to create specific programmes for everyday cognition that focus on specific training in the different instrumental activities of daily living.

It is important to point out that the short history of research in everyday cognition makes it difficult to carry out an intervention based on scientific evidence. Regarding assessment tests, it should be noted that more and more researchers support the validity of the use of assessments based on everyday cognition for the study of older people with and without cognitive impairment, being a good predictor for the diagnosis and prognosis of neurodegenerative disease [30,31].

### Limitations

The study follows all CONSORT recommendations, however, due to the nature of the intervention the principal investigator is the same person who will carry out the intervention process. However, the participants will be blinded. And, in addition, to minimise any contamination between groups, the researchers responsible for randomisation, assessments and analysis will be blinded.

### Dissemination plan

Dissemination of the results of the study will be carried out with the intention of ensuring maximum visibility. The results will be published in open access scientific journals. There will be an initial publication of the primary results and the publication of secondary results is foreseen. The results will also be presented at national and international conferences and seminars.

### How potential changes in the study will be approached

Significant modifications to the protocol (such as changes to the assessment tools, modifications to the selection criteria or to the interventions) shall be reported immediately to the bioethics committee for approval.

## Conclusions

This manuscript presents the protocol of a study aimed at evaluating the outcomes of an intervention model based on everyday cognition training on cognitive performance, functioning, emotional state and frailty in cognitively unimpaired older adults.
